#### Stratification by patient characteristic

Participants will be stratified according to three indications for treatment: simple lengthening, lengthening with deformity correction, and soft tissue correction. The amount of lengthening anticipated will be calculated both as an absolute value in cm as well as a percentage of the length of the bone to be lengthened. Amount of deformity correction will be calculated in number of degrees. Participants will be stratified to two categories according to the severity of the limb length discrepancy or deformity correction: < 20% or > 20% of the pre-operative values.

#### Potential Confounding Variables and Other Measurements

Information on infections will be recorded. All relevant concomitant medications will be recorded. These variables will be considered in exploratory analyses.

### 2. Randomization

The randomization occurs at each site according to the procedure successfully used during the pilot. The bio-statistician consultant will generate a computerized block randomization schedule for each site ensuring an equal number of subjects in each group at each site. The coordinating site will provide each site with a set of sealed envelopes containing the randomization code for each patient, which will be opened only by the individual preparing the syringe. The patients will be randomly assigned to either the treatment group or the placebo group. Concealment of randomization will be enforced, so that individuals enrolling patients will be unaware of whether the next patient will be randomized to treatment or control [73,74].

### 3. Masking

As the injection will be done intraoperatively, the patient will be blinded. The treating surgeon will be given a syringe for the injection and the surgeon will not know whether the syringe contains BTX-A or placebo. Parents, nursing staff, research, and rehabilitation staff are also blinded to group assignment. All the personnel involved in the assessments and analysis of the data will be blinded. Only the pharmacy or OR nurse preparing the syringe is aware of the group assignment.

### 5. Ethical Approval

Ethical approval was obtained from Shriners Hospital for Children Headquarters Medical Research Office and from 6 local Institutional Review Board (IRB). The research proposal will be explained to the patient and his or her family. Signed informed consent and assent will be obtained.

### 6. BTX-A Injection Protocol

#### i. Timing of the injections

The surgical procedure will be performed in the usual manner. The injection will be performed intraoperatively under general anaesthesia at the conclusion of the surgical procedure just prior to extubation to avoid any potential effects of the depolarizing agents used at the time of induction. BTX-A will be given only once (during the surgery) and will not be repeated. The advantages of giving the injection during the surgery (versus before or after) are twofold: First it will allow the analgesic action of BTX-A to take effect immediately (which is desired), while the paralytic action of BTX-A will take about 7 to 10 days to take effect (coinciding with the start of distraction). Second, the patient will be blinded and will not know whether he has or has not received the injection.

#### ii. Dosage

- The dosage will be 10 units per Kg. not to exceed 400 Units

- The maximum will be 50 units per injection site

- Maximum dose of 5 Units/kg per large muscle group not to exceed 200 Units

- Maximum volume of 1 ml per injection site

- Dilution is 100 units per ml.

This dosage is recommended by the FDA and is within the accepted range recommended by Shriners Botox Task Force as well as the American Academy of Cerebral Palsy and Developmental Medicine. Although some authors have used higher doses of BTX-A, we believe that higher doses may weaken the muscles such as rehabilitation and early weight bearing might become a problem, thus defeating the purpose of the injections.

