**Methods/Design:**

The study design consists of a multi centre, randomized, double-blinded, placebo-controlled trial. Patients between ages 5–21 years requiring limb lengthening or deformity correction using distraction will be recruited from 6 different sites (Shriners Hospital for Children in Montreal, Honolulu, Philadelphia and Portland as well as DuPont Hospital for Children in Wilmington, Delaware and Hospital for Sick Children in Toronto, Ont). Approximately 150 subjects will be recruited over 2 years and will be randomized to either receive 10 units per Kg of BTX-A or normal saline (control group) intraoperatively following the surgery. Functional outcome effects will be assessed using pain scores, medication dosages, range of motion, flexibility, strength, mobility function and quality of life of the patient. IRB approval was obtained from all sites and adverse reactions will be monitored vigorously and reported to IRB, FDA and Health Canada.

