#### Inclusion Criteria

1. Age: 5 to 21 years.

2. Etiology of the deformity: congenital or acquired.

3. Amount of lengthening or deformity correction: any amount.

4. Site of lengthening or deformity correction: lower extremity, unilateral single segment.

5. Type of fixator: circular or uniplanar.

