#### iii Dosage Calculation

Calculate maximum dose allowed according to child's weight. For example, a 40 kg patient could receive the maximum dose of 400 units.

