#### iv: Number and location of Injection Sites

Calculate the number of injection sites according to the maximum dose distributed. Agent will be injected into the bellies of the muscle groups adjacent to the bone lengthened according to the following guidelines. Diagrams for anatomical location are included in study manual.

Femoral Lengthening:

Quadriceps muscle group: (max 200 Units)/50 Uper site = 4 sites

1. Vastus Medialis (1)

2. Vastus Lateralis (1)

3. Vastus Intermedius/Rectus Femoris (2)

Hamstrings muscle group: (max 200 Units)/50 Uper site = 4 sites

1. Medial Hamstrings (4)

Tibial Lengthening/Correction:

Gastrocsoleus Muscle group: (max 200 Units)/50 Uper site = 4 sites

1. Gastrocnemius (2)

2. Soleus (2)

Clubfoot correction:

Gastrocsoleus Muscle group (max 200 Units)/50 Uper site = 4 sites

1. Gastrocnemius (2)

2. Soleus (2)

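### The stated 10 units/kg can be given only for femoral lengthening; for tibial and clubfoot procedures the protocol's own limits allow half of it

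*Protocol article*

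**What the plan says.** The abstract of the protocol article (Methods/Design) says that subjects "will be randomized to either receive 10 units per Kg of BTX-A or normal saline". Section 6, ii. Dosage, repeats this with a ceiling: "The dosage will be 10 units per Kg. not to exceed 400 Units". Neither statement is tied to a procedure. Section 6, iii Dosage Calculation, works from body weight and illustrates that "a 40 kg patient could receive the maximum dose of 400 units", again without naming a segment.

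The list in ii. Dosage also sets a tighter limit: "Maximum dose of 5 Units/kg per large muscle group not to exceed 200 Units". It allows at most 50 units and 1 ml per injection site, at a dilution of 100 units per ml.

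Section 6, iv, maps the injections. Femoral lengthening has two muscle groups, quadriceps and hamstrings, each with four sites and a 200-unit maximum. Tibial lengthening or correction has one: "Gastrocsoleus Muscle group: (max 200 Units)/50 Uper site = 4 sites". Clubfoot correction has the same single group with the same limit.

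Two other statements close off alternatives. The Inclusion Criteria require: "Site of lengthening or deformity correction: lower extremity, unilateral single segment". Section 6, i, says "BTX-A will be given only once (during the surgery) and will not be repeated".

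**The concern.** The headline dose and the limits agree for one of the three mapped procedures and conflict for the other two. A tibial or clubfoot patient cannot receive 10 units/kg without breaking the muscle-group cap, and no section says that these patients are meant to receive less.

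Two things are at stake. The first is the description of the randomised treatment: a pooled result would be read as the effect of 10 units/kg when part of the arm can receive at most 5. The article's own background says that the toxin's effects depend on dose (Mechanism of action, A) and that total dose per session was associated with adverse events and functional change (Safety, Risks and adverse effects), so the label matters.

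The second is preparation of the syringe. Under section 3, Masking, "Only the pharmacy or OR nurse preparing the syringe is aware of the group assignment", and the blinded surgeon is handed the result. A syringe drawn up from the headline dose and the weight-based example would hold twice what is permitted for a tibial or clubfoot case. The same section 6 argues against higher doses because weakened muscles could hinder rehabilitation and early weight bearing.

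**Working it through.** **Inputs, all from section 6.** With *w* the weight in kg:

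- stated total: 10 units/kg, maximum 400 units (ii)
- group cap: 5 units/kg, maximum 200 units (ii)
- site limits: 50 units and 1 ml; dilution 100 units/ml (ii)
- groups mapped: two for the femur, one for tibia, one for clubfoot, with four sites each (iv)

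**Formulas.**

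- Stated dose = min(10*w*, 400).
- Permitted dose = number of groups × min(5*w*, 200, 4 × 50).

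**The plan's own figure.** At 40 kg the stated rule gives min(400, 400) = 400 units, as in the example. The femoral map reproduces it: 2 × min(200, 200, 200) = 400. The tibial and clubfoot maps do not: 1 × 200 = 200.

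**Other weights.**

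| Weight (kg) | Stated (units) | Femur permitted (units) | Tibia/clubfoot permitted (units) | Femur vs tibia/clubfoot (units/kg) |
|---|---|---|---|---|
| 20 | 200 | 200 | 100 | 10 vs 5 |
| 30 | 300 | 300 | 150 | 10 vs 5 |
| 40 | 400 | 400 | 200 | 10 vs 5 |
| 60 | 400 | 400 | 200 | 6.7 vs 3.3 |

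The ratio is 2 throughout. The 1 ml limit does not bind, since 50 units is 0.5 ml.

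**Would the injection map catch the error?** Take a tibial patient of 20 kg (assumed; weights are not given, but entry is from age 5) and a dose set from weight alone:

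- total: 10 × 20 = 200 units (limit printed in the map: 200)
- per site: 200 / 4 = 50 units (limit 50)
- volume per site: 2.0 / 4 = 0.5 ml (limit 1)
- group dose: 200 / 20 = 10 units/kg (cap 5, so 100 units permitted)

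Only the last limit is broken, and the map does not print it. At 30 kg the weight-based 300 units does exceed the map's 200, but trimming to 200 still exceeds the permitted 150. From 40 kg upwards 5 units/kg is at least 200 units, so the printed 200-unit limit is enough.

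**Mean dose in the active arm.** The segment mix is not given. With a share *p* of tibial and clubfoot patients (assumption), the ceiling on mean dose in patients up to 40 kg is 10(1 − *p*) + 5*p* = 10 − 5*p*:

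- *p* = 0.25: 8.75 units/kg
- *p* = 0.50: 7.5 units/kg
- *p* = 0.75: 6.25 units/kg

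I draw no conclusion about power, because the article gives no dose-response relation from which to derive one.

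**The case against.** The strongest reply is that the dosing section is a set of joint limits in which the tightest governs. The group cap stands in the same list as the headline dose, the map prints the 200-unit maximum under both the tibial and the clubfoot headings, and the rules taken together give one permitted maximum per procedure. The dosage calculation speaks of a maximum that a patient could receive, and the 400-unit ceiling already takes femoral patients above 40 kg below 10 units/kg, so 10 units/kg may be read as a ceiling. Dose per muscle group is the same in every segment, which is a coherent design. No section says that the syringe is prepared from weight alone, and a study manual covering injection exists (section 12, Standardization) but is not shown.

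Much of this stands. The limits can be combined, the caps protect patients if followed, the per-group dose is consistent, and misdosing is a possibility rather than something the protocol prescribes.

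The ceiling reading does not remove the conflict. The abstract and ii. Dosage present 10 units/kg as the dose to be given. Even as a ceiling it is wrong for tibia and clubfoot, where the ceiling is 5 units/kg and 200 units. The manual might prevent misdosing, but it would not correct what the article states.

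**Conclusion.** The concern holds. The unqualified dose of 10 units/kg, maximum 400 units, is correct only for femoral lengthening. For tibial and clubfoot procedures the protocol permits half of it at every weight. This follows from the printed limits alone, counting the gastrocsoleus as one group, as the article labels it.

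The 20 kg and 30 kg illustrations and the mean-dose figures rest on assumed weights and an assumed segment mix; the factor of two does not. The randomised comparison is not biased, and design, sample size and analysis model are unaffected. What is wrong is the description of the treatment, together with a dosing ambiguity that is greatest for the smallest children. It should be fixed.

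**What to change.** - In the abstract and in ii. Dosage, state the dose by segment. If the present limits express the intent: femoral 10 units/kg, maximum 400 units; tibial and clubfoot 5 units/kg, maximum 200 units.
- In iii Dosage Calculation, restrict the 40 kg, 400-unit example to femoral cases.
- In iv, print both parts of the cap (5 units/kg, maximum 200 units) beside each muscle group.
- In the results, report units/kg given by segment alongside the analysis by site of fixator.

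The cost is a few words in four places and one descriptive line. The dose given is already recorded (section 10, Data Safety and Monitoring Committee), and stratification by site of fixator is already foreseen (Secondary Analysis).

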#### iii Dosage Calculation

Calculate maximum dose allowed according to child's weight. For example, a 40 kg patient could receive the maximum dose of 400 units.

#### iv: Number and location of Injection Sites

Calculate the number of injection sites according to the maximum dose distributed. Agent will be injected into the bellies of the muscle groups adjacent to the bone lengthened according to the following guidelines. Diagrams for anatomical location are included in study manual.

Femoral Lengthening:

Quadriceps muscle group: (max 200 Units)/50 Uper site = 4 sites

1. Vastus Medialis (1)

2. Vastus Lateralis (1)

3. Vastus Intermedius/Rectus Femoris (2)

Hamstrings muscle group: (max 200 Units)/50 Uper site = 4 sites

1. Medial Hamstrings (4)

Tibial Lengthening/Correction:

Gastrocsoleus Muscle group: (max 200 Units)/50 Uper site = 4 sites

1. Gastrocnemius (2)

2. Soleus (2)

Clubfoot correction:

Gastrocsoleus Muscle group (max 200 Units)/50 Uper site = 4 sites

1. Gastrocnemius (2)

2. Soleus (2)

### 7. Adverse Events

All serious adverse experiences will be reported. Minor adverse events and unusual complications encountered during the lengthening and or correction process will be carefully recorded. Side effects include a flu-like syndrome that is generally short-lived, dysphagia, and dry mouth. Unintended weakness of the muscle injected or of nearby muscles could also be a negative effect. Other side effects include muscle soreness, rash, headaches, light-headedness, fever, chills, hypertension, diarrhea and abdominal pain.

In the event of a serious adverse reaction to the treatment the patient will be treated accordingly depending on the reaction. The following events will cause immediate cessation of the study.

1. Death

2. Upper limb paralysis or weakness

3. Bulbar weakness

a. Blurred vision

b. Facial paralysis

c. Dysarthria

4. Anaphylactic reaction

5. Any severe ADR

Unblinding of the patient will be carried out immediately. The event will be analyzed in the same manner as any severe ADR. This will be reported to the appropriate agencies with the analysis, conclusions and recommendations. The study will then be re-instituted if given approval to continue. This patient will be categorized as a treatment failure and assigned (imputed) the most negative score on all outcomes.

### 8. Pain Management Protocol

Pain management (assessment and treatment) guidelines are described in the study manual. Post operative pain medication is delivered via either PCA or epidural up to 72 h post-op. Pain assessment will be done using a 10 point scale (either Faces Pain Scale revised or the Numerical Rating Scale) according to post-operative PCA protocols; hourly for first 4 hours, every 2 hours for next 8 hours, and every 4 hours once stable. After the PCA/epidural is discontinued, PRN medications will be ordered for pain control, nausea/vomiting, itching, and fever during hospitalization. Pain assessments will also be done whenever a patient receives a PRN medication. All of this data will be recorded in the patient's chart along with the medication dosages administered.

### 9. Post operative Activity and Rehabilitation Regimes

Patients will stay in hospital for 4–7 days following application of the external fixator and administration of the botox/placebo and until they are independent with the turnings. During this period patients will follow the pain management guidelines suggested for this group. All patients will also be seen by a physical therapist for a standardized exercise regime. During the distraction phase patients will be followed in clinic on a biweekly basis and during the consolidation phase on a monthly basis. The children will continue to be followed for three months after the external fixator is removed. Pain management, physical therapy, radiographs and adverse event assessment will continue during the entire lengthening process. Physical therapy and pain protocols are outlined in a study manual.

### 10. Data Safety and Monitoring Committee (DSMC)

A Data and Safety Monitoring Committee (DSMC), consisting of two experts in orthopedics and one biostatistician, will be constituted of experts with no vested interest in the trial. The DSMC will be responsible for supervision of the interim analysis, monitoring of the trial, and review of all adverse events. The study will be stopped if the interim analysis shows statistically significant results.

The study is blinded to the physician and assessors of outcomes. The pharmacist at each center is responsible to track each patient in the study, record which medication was injected, and the clinical staff will record any adverse effects noted. A standard data collection sheet will list each patient, the dosage given and any adverse outcomes. The information will be collected concurrently during the immediate post-injection period with each local co-investigator informed of any adverse effects. **For safety, the investigators at each participating center will have access to which medication is injected if treatment of an acute adverse event is necessary**. They will update the information to the PI on a weekly basis as needed. The PI and clinical staff are responsible for monitoring patient safety by tracking and collating the data from all participating centers. All adverse effects will be reported to the appropriate oversight committees (local IRB and FDA). The PI is responsible to communicate these findings and any changes in protocol as needed to the co-investigators.

### 11. Outcome Assessment

The outcome measures selected for the study relate directly to the specific aims of the project. The data collected will provide information on the pain scores, medication dosages, range of motion, flexibility, strength, mobility function, and quality of life of the patient population under study. Additional data will be collected on the patient demographics, musculoskeletal information, impact on the family during the distraction process, and motivation of the child. During the pilot study the participating hospitals finalized the selection of the outcome tools, the data collection forms of physiotherapy and nursing, as well as the timing of administration. The research coordinator at each site will ensure that the timeline is respected.

The measures will be administered pre-lengthening, pre-distraction, mid-distraction, end distraction, mid-consolidation, pre-frame removal and 3 months post-frame removal. Pain scores, medication dosages and compliance to physical therapy will be recorded daily during admission and throughout the distraction/consolidation process. A timeline as shown in Table 1 will indicate when the different variables will be measured and which tool is given at which phase of the process. The time required to complete the assessments is 20–30 minutes.

Standardized assessments chosen have been validated and are reliable. The outcome measures are described below.

The **Numerical Rating Scale (NRS**) is a reliable and valid tool that is widely used in pediatric centers as a measure of acute pain. The **Faces Pain Scale-Revised **is a reliable and valid pain scale for younger children. These tools will be used by nursing to assess postoperative pain during the first 5–7 days following surgery. The same scale will be used by physiotherapists to assess pain pre and post-physiotherapy treatment. In addition patients will be familiar with these scales and will use them to rate their pain in a Pain/Medication/PT compliance journal throughout the study. The NRS has been translated into several languages. Guidelines accompany both the NRS and Faces Pain Scale-Revised ensuring that they are administered in a uniform fashion [75].

**Medication dosages **are extracted from the inpatient medical record and recorded on custom data collection forms. The pain scores from the inpatient and outpatient period are also transcribed to this form.

The **Adolescent Pediatric Pain Tool (APPT) **is a three part tool which includes a visual analogue scale, a listing of 42 words that describe pain qualitatively and body diagrams to localize the pain. Its validity and reliability have previously been established. Furthermore, this tool was previously used in the only other study on pain during treatment of limb length discrepancy [15,76,77] The APPT will be administered at the key pre-determined intervals to measure the current, pain underlying the lengthening procedure and in particular during the distraction phase.

The **active and passive range of motion (ROM) **of involved joints will be measured using a goniometer according to the Shriners Hospital for Children Motion Analysis Lab ROM protocols in order to evaluate the effect of BTX-A on muscle spasm and muscle contracture (Specific aim 2). Measurement will be recorded by the treating physical therapist as of post-op day 2, continuing daily until discharge, weekly during distraction and monthly during consolidation. Standard flexibility tests using measurements of angles will also be recorded. **Strength **will be measured by active movement and by the extent of the quads lag at baseline and at 3 months post frame removal.

The **Gillette Functional Assessment Questionnaire (FAQ) **was developed by the Gillette Children's Specialty Healthcare to measure ambulation status. The pre-op version includes a 10-level parent report walking scale, need for assistive devices, and lists to describe limits to walking and additional activities commonly performed in the standing position. The walking scale only will be administered according to the timeline. The inter and intra rater reliability of the walking scale has previously been demonstrated as well it is sensitive to changes in orthopedic conditions.

The **Pediatric Quality of Life Inventory (PedsQL) **is a 23-item questionnaire developed by Dr. J. Varni at the Center for Child Health Outcomes at the Children's Hospital and Health Care Center, San Diego. According to the authors, the PedsQL measures health related quality of life in healthy children and children with health conditions. The generic module which consists of four domains: physical health, emotional, social, and school, as well the pain section (4 items) of the rheumatology module, will be administered to assess quality of life during the lengthening or correction process. The PedsQL has a parent and child version for five different age groups and so measures both perspectives of the impact of the procedure. It is self-administered and has been translated into French and Spanish. Completion requires 10 minutes. The PedsQL has proven reliability and validity and can distinguish between healthy children and those with health conditions. [78].

The **Impact on Family Scale (IOF) **is a 27-item inventory translated into French and Spanish that takes approximately 10 minutes to complete and measures a parent's perception of the effects of the child's ongoing health condition on family life. The IOF will measure the amount of stress and disequilibrium experienced by the family of the child undergoing the painful and long lengthening or correction. It will be administered at the end of the process. It is not disease specific and can be used with minimal training. The measure has been widely used since 1980 and has good face validity. It has recently undergone a revised scoring procedure and additional psychometric tests showing that it is a reliable and valid measure [79].

The **Dimensions of Motivation Questionnaire (DMQ-17) **was developed by Morgan, Maslin-Cole, Biringen and Harmon to measure motivation, a multi-faceted, intrinsic psychological force that stimulates an individual to attempt to master a skill or task that is at least moderately challenging for him. The DMQ was recently revised to include all ages of children. It consists of a 45-item questionnaire of 5 scales: object oriented persistence, social/symbolic persistence, gross motor persistence, mastery pleasure, and general competence. The DMQ will measure a child's underlying motivation to determine what role it may play in the outcome of lengthenings. The recent re-scoring of the DMQ has produced a conceptually stronger and psychometrically stronger questionnaire [80,81].

A **Pain**/**Medication/PT Compliance Journal **will record the amount of analgesic medication required daily (dosage, frequency, time), pain experienced and compliance to Physical Therapy home exercise program during the outpatient period. The family will be provided with a customized booklet for this purpose.

**Radiographs **will be obtained during the process to assess the amount of lengthening, state of new bone formation, quality of the regenerate, and development of osteopenia.

